#### Primary Hypotheses

The primary hypotheses are as follows:

Facilitated WhatsApp support groups (yes or no): we hypothesize that parents receiving the ParentText delivery package combined with web-based support via WhatsApp groups will have higher engagement rates than those receiving the ParentText delivery package without facilitated support via WhatsApp groups.In-person sessions (1 or 4 sessions): we hypothesize that parents receiving the ParentText delivery package combined with 4 in-person sessions will have higher engagement rates than those receiving the ParentText delivery package with 1 in-person session.Incremental cost-effectiveness: we hypothesize that, while the inclusion of facilitated WhatsApp groups will be more cost-effective than not including facilitated WhatsApp groups based on the incremental cost advantage, the higher dosage of in-person sessions will not be a cost-effective component.

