#### Cost-Effectiveness Analysis

This study will evaluate the efficiency and affordability that results from the expansion or contraction of the ParentText delivery package from the provider’s perspective. Program implementation costs and outcome data will be recorded and analyzed in Excel. The total costs of the intervention (setup and operating costs) for each intervention component and the average cost per participant enrolled (unit cost) will be estimated. The trial’s primary outcome relates to levels of user engagement (ie, the overall number of modules completed by participants), and this will be used to understand the cost-effectiveness of the intervention components that will maximize user engagement with ParentText. The estimated cost-to-engagement ratio for each of the intervention components will be calculated and compared to assess the incremental cost-effectiveness of each component. All costs will be adjusted to 2023 US dollars using the Consumer Price Index.

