#### Analytical Strategy for Selecting the Most Optimal Intervention Package

We will use the decision-making framework presented by Collins [52] to select the most effective, cost-effective, and feasible components and component levels for inclusion in the optimized intervention before testing in a randomized controlled trial. As shown in Figure 3, the most optimal intervention package will be the one presenting higher effectiveness while considering resource and feasibility constraints. First, the main effects of each component on primary engagement outcomes will be identified and averaged across the other intervention components. Second, intervention components will be divided into a screened-in and screened-out set based on their positive effectiveness on participants’ engagement with ParentText. Intervention components with negative or no effect will be included in the screened-out set, and the lower level of that component will not be considered further. Third, intervention components in the screened-in set (ie, those showing positive effects and cost-effectiveness) will be considered for further evaluation. Results from qualitative interviews and focus group discussions conducted with the implementing partner will be used to further understand the feasibility, acceptability, effectiveness, and cost-effectiveness of the retained component levels and draw conclusions to develop the final optimized ParentText delivery package.

The posterior expected value approach will be included in the decision-making process to increase the robustness of our results. In previous research, the posterior expected value approach has modestly outperformed the component screening approach in accuracy, sensitivity, and specificity [94]. Estimates of the posterior expected value for each intervention component will be obtained using Markov chain Monte Carlo methods. We will prefer intervention components with higher Markov chain Monte Carlo posterior distribution of mean outcomes.

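### The screened-in set is defined by engagement effect alone in one step and by effect plus cost-effectiveness in the next, and the two disagree for the result hypothesised for 4 in-person sessions

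*Protocol article*

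**What the plan says.** The rule is in the Protocol article, under Analytical Strategy for Selecting the Most Optimal Intervention Package. Its stated aim is that "the most optimal intervention package will be the one presenting higher effectiveness while considering resource and feasibility constraints". Three steps follow.

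- First, main effects on the primary engagement outcome are estimated, averaged over the other component.
- Second, "intervention components will be divided into a screened-in and screened-out set based on their positive effectiveness on participants’ engagement with ParentText". The opposite set is described next: "Intervention components with negative or no effect will be included in the screened-out set". The same sentence adds that the lower level of such a component drops out of consideration.
- Third, "intervention components in the screened-in set (ie, those showing positive effects and cost-effectiveness) will be considered for further evaluation". Qualitative interviews and focus groups then inform judgement on the component levels that were retained.

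Under Cost-Effectiveness Analysis, the comparison is described as follows: "The estimated cost-to-engagement ratio for each of the intervention components will be calculated and compared to assess the incremental cost-effectiveness of each component".

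Under Primary Hypotheses, parents receiving the package "combined with 4 in-person sessions will have higher engagement rates than those receiving the ParentText delivery package with 1 in-person session". The third primary hypothesis adds that "the higher dosage of in-person sessions will not be a cost-effective component".

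**The concern.** The second and third steps describe one set with two membership rules. The second uses the engagement effect alone. The third, through the word *ie*, says that membership means a positive effect together with cost-effectiveness. A component that raises engagement but is not cost-effective is inside the set by one sentence and outside it by the other.

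The trial exists to choose the package for the randomized trial planned for 2024. Only screened-in components are taken further, and the qualitative and feasibility material is applied to what has been retained. Set membership therefore decides whether a component's higher level reaches that review. If the wording stays as it is, the choice between the two rules can be made after the results are known.

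**Working it through.** No arithmetic applies, and no figure in the Sample Size section bears on the point. The check is to apply each definition to every possible result for a component.

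**Definition A** (second step): in if the effect on engagement is positive, out if it is negative or absent.

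**Definition B** (third step): in if the effect is positive and the component is cost-effective.

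| Positive effect on engagement | Cost-effective | A | B | Agree? |
|---|---|---|---|---|
| Yes | Yes | In | In | Yes |
| Yes | No | In | Out | **No** |
| No | Yes | Out | Out | Yes |
| No | No | Out | Out | Yes |

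The definitions differ in one combination of four.

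The next question is whether that combination is expected. The Primary Hypotheses give two statements about 4 in-person sessions against 1: engagement will be higher, and the higher dosage will not be cost-effective. Together they place the in-person component in the second row of the table. For WhatsApp groups the hypotheses are higher engagement and better cost-effectiveness, which is the first row, where the definitions agree. If the stated hypotheses hold, one of the two tested components receives two different classifications.

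Three other parts of the document could in principle settle which definition governs:

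- The screened-out set is described only by a negative or null effect. It has no place for a component that works but is not cost-effective, so Definition B leaves that component in neither set.
- Cost-Effectiveness Analysis says that ratios are calculated and compared. It does not say whether that comparison belongs to screening or comes after it.
- The posterior expected value approach is added for robustness and prefers higher posterior mean outcomes. As described, it does not involve cost and does not say which screening definition applies.

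The sentence on the lower level also needs attention. Every condition in Table 1 includes at least the one onboarding session, and the lower level of the WhatsApp component is no group. A component whose higher level is not retained can then only continue at its lower level. Yet the text says that for a screened-out component it is the lower level that is not considered further.

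**The case against.** The strongest reply is that the steps are numbered and meant as successive filters. On that reading the second step sorts on effect, the third removes what is not cost-effective, and the overall aim names effectiveness, cost-effectiveness and feasibility together. This is plausible and may be what the authors intend. It is not what the text says, because *ie* restates the membership of a set already formed and adds no filter. Figure 3 is not available here and may order the steps, but the two sentences conflict whatever it shows.

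A second reply is that the final package may be the same either way, since cost-effectiveness also informs the review of the retained levels. This stands in part. A reader might infer that the contradiction must change the package selected. The documents do not support that. What differs is whether the higher level reaches the review at all.

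Two other stronger readings are also unsupported.

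- A reader might take the 80% or 90% power in the Sample Size section as the probability that the two rules conflict. That would only restate the design power. It also assumes that screening requires significance at the 10% level, which the selection strategy does not state, and that cost-effectiveness always comes out unfavourable. A larger observed effect also improves the cost-to-engagement ratio, so the two results are not independent.
- A reader might fault the absence of a numerical cost-effectiveness cut-off. A condensed article may leave that to the full protocol or analysis plan, so it is not a finding here.

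**Conclusion.** The contradiction is real and can be confirmed from adjacent sentences. It is confined to one kind of result, effective but not cost-effective, and that is the result the primary hypotheses predict for the in-person component. The consequence is an ambiguous decision rule: whether the higher level proceeds to the qualitative and feasibility review depends on the sentence chosen. Estimates, tests and error rates are unaffected.

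The conclusion rests on reading *ie* as a definition, which is its ordinary meaning, and on the review being limited to retained component levels, as the text says. It does not depend on sample size, power or intracluster correlation. Correction is worthwhile because the rule serves the trial's stated purpose and the change costs almost nothing.

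**What to change.** Before unblinding, settle on one definition of the screened-in set and use it throughout. One coherent option is:

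1. Define the set by the effect criterion of the second step.
2. Delete the reference to cost-effectiveness from the parenthesis in the third step.
3. State cost-effectiveness, judged by the planned cost-to-engagement comparison, as a separate later step applied to the screened-in components, and say what happens to a component that does not pass it.

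Keeping the narrower definition would also be consistent, provided that the second step and the description of the screened-out set were changed to match.

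In the same edit, reconcile the sentence that removes the lower level of a screened-out component with a rule under which a component that is not retained goes forward at its lower level. The numerical criterion for cost-effectiveness can sit in the full analysis plan.

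The cost is the rewording of a few sentences. No new data, analysis or sample is needed.

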**Figure 3 figure3:**
[figure not shown]
Analytical strategy for selecting the most optimal intervention package for evaluation in a subsequent randomized controlled trial.

#### Interim Analyses

No interim analyses will be conducted.

#### Methods for Additional Analyses

Exploratory analysis will examine the effect of cultural determinants on parents’ behavioral intention to use ParentText. Pearson correlations will be used to determine the relationship between cultural determinants (perceived ease of use, perceived usefulness, hedonic motivation, habit, price value, and social influence) and behavioral intention toward ParentText use. Multiple regression analysis will be used to investigate the strength of the association between cultural determinants and behavioral intention and between behavioral intention and primary and secondary engagement outcomes. Predictive models will be used to investigate how behavioral intention predicts parents’ primary and secondary engagement outcomes.

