#### Secondary Hypotheses

The secondary hypotheses are as follows:

Behavior outcomes: we hypothesize that the most intensive combination of component levels will have the greatest effect on parent and adolescent behavioral, mental health, and education outcomes.Cultural determinants: we hypothesize that cultural determinants (perceived ease of use, perceived usefulness, hedonic motivation, habit, price value, and social influence) will be associated with more favorable intentions to engage with ParentText.Behavioral intention: we hypothesize that more favorable intentions to engage with ParentText will lead to higher primary and secondary engagement rates.

The positive directionality of the effects of the 2 intervention components on engagement outcomes will be preferred in this study due to evidence of the positive impact of engagement boosters in parenting interventions [53,54]. No hypotheses will be made a priori for potential moderators of effectiveness or cost-effectiveness.

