##### Engagement Outcomes

Baseline differences between groups will be described using proportions, means, and SDs. The main effect of each intervention component and interaction effects between components on primary and secondary engagement outcomes will be estimated using multilevel models (including mixed models if outcomes are continuous, Poisson models if outcomes are counts or count distributed, and logistic models if outcomes are binary). Separate models will be tested using effect coding [91,92]. Each model will specify 3 levels to account for the longitudinal and clustered nature of the data—repeated measures are nested within individuals, which are, in turn, nested within clusters. Level 1 will include a term for categorical time (pre- and posttest time points) and for the interaction between time and intervention status, level 2 will include terms for individual sociodemographics such as age (parent and adolescent) and gender (parent) and other individual-level covariates centered at the sample mean, and level 3 will include terms for the intervention components and the stratifying factor. Robust SEs will also be estimated to adjust for clustering. This study will report the direction and magnitude of β, incidence risk ratios, and odds ratios at a significance level of *P*<.10 with 90% CIs. Two-tailed tests will be conducted across all analyses.

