#### Moderation Analyses

In addition, the study will use regression analysis and multilevel regression models to investigate the following: (1) which adult baseline characteristics moderate the effect of the intervention components on primary and secondary engagement outcomes and (2) which adult baseline characteristics moderate the effect of the intervention components on parent and adolescent behavioral, mental health, and educational outcomes.

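### No provision for clustering is stated for the correlations and regressions that address two secondary hypotheses, so their 90% CIs may be too narrow

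*Protocol article*

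**What the plan says.** Methods for Additional Analyses fixes the methods for two relations. For determinants and intention it states "Pearson correlations will be used to determine the relationship between cultural determinants" and intention, and then "Multiple regression analysis will be used to investigate the strength of the association between cultural determinants and behavioral intention". The same regression sentence extends to intention and the engagement outcomes, and a further sentence assigns unspecified predictive models to that second relation. The section mentions no cluster term, robust standard error or intervention component.

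The other quantitative sections do allow for clustering:

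- Engagement Outcomes sets out multilevel models with the components and the stratifying factor at cluster level, Poisson models for counts, and "Robust SEs will also be estimated to adjust for clustering".
- Behavioral, Mental Health, and Educational Outcomes uses the same models and allows for clustering even in its within-group comparisons.
- Moderation Analyses says "the study will use regression analysis and multilevel regression models to investigate the following".

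The status of the two relations is mixed. Secondary Hypotheses lists both: the determinants "will be associated with more favorable intentions to engage with ParentText", and "we hypothesize that more favorable intentions to engage with ParentText will lead to higher primary and secondary engagement rates". Secondary Objectives words both in terms of significant contribution. Methods for Additional Analyses, however, opens with "Exploratory analysis will examine the effect of cultural determinants on" intention.

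**The concern.** Parents are recruited, onboarded and surveyed within 32 clusters, each with its own facilitator. Determinants and intention are collected straight after the in-person onboarding session, and engagement then accrues under that same facilitator. Shared session and facilitator effects could therefore move the predictor and the outcome together. A standard Pearson P value or CI treats every parent as independent, and so does a multiple regression with default standard errors.

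Two hypothesis-level statements would then rest on intervals that overstate precision, at a significance level already set at 10%. Intention versus engagement raises a second question. Engagement is what the randomised components are meant to raise, participants know their own allocation (Who Will Be Blinded), and randomisation precedes baseline. If intention differed by arm, a slope without the component terms would mix the effect of allocation with the effect of intention.

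**Working it through.** **The plan's own figure.** Sample Size is the only place where clustering enters a calculation. Inputs: 32 clusters of 60 parents, so 16 versus 16 clusters and 960 parents per level of a main effect; two-sided 10% level; ICC 0.02 to 0.10; SD 1.

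Design effect = 1 + 59 × ICC, which gives 2.18 at 0.02 and 6.90 at 0.10. MDE = (1.645 + z for power) × √(2 × design effect / 960).

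- 80% power: 2.487 × √(2 × 2.18/960) = 0.168; 2.487 × √(2 × 6.90/960) = 0.298.
- 90% power: 2.927 × √(2 × 2.18/960) = 0.197; 2.927 × √(2 × 6.90/960) = 0.351.

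All four agree with the protocol.

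**The associations.** For the slope of a predictor measured on each parent, the variance inflation that a naive analysis misses is about

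1 + (m − 1) × ICCx × ICCy,

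and a nominal 90% CI truly covers 2Φ(1.645/√inflation) − 1.

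Inputs: m = 60 (planned), or m = 744/32 = 23.25 (caregivers who completed onboarding, from the abstract's Results, assumed spread evenly over 32 clusters). ICCy is taken over the protocol's range. ICCx is not in the documents and is assumed equal to ICCy.

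| m | Both ICCs | Inflation | SE factor | True coverage |
|---|---|---|---|---|
| 60 | 0.02 | 1 + 59 × 0.0004 = 1.024 | 1.012 | 89.6% |
| 60 | 0.05 | 1 + 59 × 0.0025 = 1.147 | 1.071 | 87.5% |
| 60 | 0.10 | 1 + 59 × 0.01 = 1.590 | 1.261 | 80.8% |
| 23.25 | 0.02 | 1 + 22.25 × 0.0004 = 1.009 | 1.004 | 89.8% |
| 23.25 | 0.05 | 1 + 22.25 × 0.0025 = 1.056 | 1.027 | 89.1% |
| 23.25 | 0.10 | 1 + 22.25 × 0.01 = 1.223 | 1.106 | 86.3% |

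With ICCx = 0 the inflation is 1 and coverage stays at 90%.

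**Simulation check** (32 clusters, 4,000 runs, true slope 0.20, clustering ignored). Coverage at ICCs 0.02, 0.05 and 0.10 was 89.2%, 87.8% and 80.8% with 60 per cluster, and 90.3%, 88.9% and 86.6% with 23. This agrees with the formula.

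**Component terms.** The simulation was repeated with both components shifting the outcome by 0.298 SD and intention independent of arm. With the components left out, coverage at 60 per cluster was 88.3%, 85.2% and 79.0%. The largest extra loss is 87.8 − 85.2 = 2.6 points. With the components included but clustering still ignored, it was 90.4%, 88.2% and 80.7%. The mean slope stayed at 0.20 throughout, so there was no bias under that independence.

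**The case against.** The strongest reply is that the article is condensed. Multiple regression does not exclude a random intercept, robust standard errors or a count link, and the covariates of additional analyses are commonly left to a fuller plan. Moderation Analyses uses regression and multilevel regression side by side, so the wording is loose in general. The determinants analysis is labelled exploratory, and neither relation enters the rule for selecting the optimised package.

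Much of this stands, and it rules out several stronger readings that a reader might infer:

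- **That the plan commits to ordinary linear regression.** Neither ordinary nor linear appears in the text. The supportable statement is that no provision for clustering is stated.
- **That the intervals are certainly too narrow.** The loss depends on the product of two ICCs, and one of them is not given.
- **That the error is very large.** The planning design effects of 2.18 to 6.90 apply only to a predictor that is constant within a cluster. ICCs of 0.20 lie outside the protocol's range.
- **That leaving out the components narrows the intervals or biases both relations.** Determinants and intention are both measured at the onboarding that every arm receives, so the point mainly concerns intention versus engagement. Bias there requires intention to differ by arm, which is possible but not shown.

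What does not stand is that this is only missing detail. The section names a method whose standard inference assumes independence, the robust-SE sentence belongs to a different section and is not extended to it, and the neighbouring sections all mention clustering.

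**Conclusion.** The point holds in conditional form. The named methods carry no stated provision for clustering, for two relations that the protocol lists as secondary hypotheses. The shortfall in coverage of a nominal 90% CI runs from 0.4 to 9.2 points at 60 parents per cluster (89.6% to 80.8%) and from 0.2 to 3.7 points at about 23 (89.8% to 86.3%). It is zero if the predictor does not vary between clusters. These figures assume a predictor ICC equal to the outcome ICC, the protocol's range of 0.02 to 0.10, and equal cluster sizes.

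The component and count-model points are secondary. The first guards against possible confounding of the intention slope. The second removes an ambiguity over how a module count is modelled in two sections. The primary analysis and the choice of package are unaffected, so this is a change that should be made but not a critical one.

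**What to change.** In Methods for Additional Analyses:

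1. State that the associations are estimated with a cluster random intercept or with cluster-robust standard errors, using a small-sample correction suited to 32 clusters.
2. Report the Pearson coefficients descriptively, or give them cluster-adjusted inference.
3. For intention versus engagement, add district and the effect-coded components, and use the count model from Engagement Outcomes for modules completed. Say which model the term predictive models refers to.
4. Reconcile the exploratory label with Secondary Hypotheses, so that both sections give these relations the same status.

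Centring on cluster means is optional. It changes the quantity estimated to a within-cluster association and is not needed to correct the standard errors.

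The cost is analysis wording only, with the same data and software. The protocol asks for a formal amendment for significant changes to analysis, so the team should decide whether this qualifies and record it either way.
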